## Background

Preeclampsia (PE) is a hypertensive disorder of pregnancy characterized by the de novo onset of hypertension after 20 weeks of gestation, accompanied by proteinuria or evidence of end-organ dysfunction or fetal growth restriction (FGR) [1]. Complications such as eclampsia, placental abruption and hemolysis, elevated liver enzymes, and low platelets (HELLP) syndrome leading to life-threatening conditions like liver hematoma and disseminated intravascular coagulation, make PE one of the leading causes of maternal morbidity and mortality worldwide. The incidence of PE is estimated at 2–5%, and it accounts for approximately 50,000 maternal deaths each year, 99% of which occur in low- and middle-income countries [2, 3]. Optimizing antenatal care to prevent disease progression is therefore essential to mitigate the severity and adverse outcomes associated with the disorder [4]. However, delivery remains the only definitive treatment, making early forms of PE the leading cause of iatrogenic prematurity [5, 6]. Early-onset preeclampsia (eoPE), defined as PE occurring before 34 + 0 weeks of gestation, accounts for about 20% of all cases and is associated with a tenfold increase in maternal mortality and a fourfold increase in severe maternal morbidity [7].

In eoPE, an excess of antiangiogenic factors—particularly soluble fms-like tyrosine kinase-1 (sFlt-1)—is released into the maternal circulation, reducing the bioavailability of proangiogenic factors such as placental growth factor (PlGF). The resulting angiogenic imbalance induces systemic endothelial dysfunction, which underlies the multiorgan involvement characteristic of the disease [8]. An elevated sFlt-1/PlGF ratio has been consistently associated with the onset and severity of eoPE [9] and shows an inverse correlation with the time to delivery [10]. These findings highlight the potential role of angiogenic biomarkers for improving clinical risk stratification.

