**Fig. 1 Fig1:**
[figure not shown]
Overview of the machine learning models to be validated. For each model, the classification approach, the input variables used, and the results obtained during the development phase are presented. MCAPIp5_echo: Pulsatility index in the middle cerebral artery < percentile 5; GA_PE: Gestational age at preeclampsia onset; NumDrug: Number of antihypertensive administrated drugs; PIrUtA_echo: Pulsatility index of the right uterine artery; previous_PE: Preeclampsia in previous gestations; PlGF5: Angiogenic marker < percentile 5 for gestational age according to Verlohren et al. [32]; RatioScale: Clinical classification of sFlt-1/PlGF relation (0–38: normal; >38–85: suspicion of preeclampsia; >85–655: consistent with a diagnosis of preeclampsia; >655: high-risk of preeclampsia-related complications); weight: Pre-gestational weight; EFWp_echo: Customized percentile of estimated fetal weight; PIlUtA_echo: Pulsatility index of the left uterine artery; chronic_ht: Maternal chronic hypertension; mPIUtAMoM: Multiples of the median of the mean pulsatility index of the uterine arteries; sFLt195: Antiangiogenic marker > percentile 95 for gestational age according to Verlohren et al. [32]; PlGFscale: Clinical classification of PlGF

Despite these encouraging findings, external validation in a broader and more heterogeneous population is essential before these models can be considered for clinical implementation. The present study aims to address this need assessing the diagnostic accuracy, calibration, and clinical utility of the models across multiple hospitals participating in the Spanish RICORS-SAMID network.

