### Objectives

The primary objective of this study is to externally validate the diagnostic performance and clinical usefulness of three ML–based models designed to predict (1) maternal complications, (2) the need for delivery within ≤ 7 days of diagnosis, and (3) the development of HELLP syndrome or placental abruption.

Secondary objectives of this study include:

Improvement of the prediction models by incorporating data from 100 new eoPE cases into the ML training process.Adjustment of the training process to specifically train and optimize the models for the eoPE subgroup with the greatest potential for applicability due to their clinical interest in management: PE diagnosed between 30 + 0 and 33 + 6 weeks of gestation.Conduct a semi-quantitative post-hoc assessment of healthcare professionals’ satisfaction with the information provided by the models to adjust the timing of (1) fetal maturation with corticosteroids, (2) hospitalization, and (3) pregnancy termination.Development of a web application that integrates the data collection and validation process (both quantitative and semi-quantitative) into a single tool accessible to clinicians.

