### Inclusion criteria

Eligible patients are pregnant women meeting all of the following criteria: (1) maternal age ≥ 18 years; (2) singleton pregnancy; (3) diagnosis of PE established according to the criteria of the International Society for the Study of Hypertension in Pregnancy [11]; (4) gestational age at the time of diagnosis between 20 + 0 and 33 + 6 weeks; (5) availability of angiogenic biomarker results (sFlt-1/PlGF ratio) obtained at the time of diagnosis (± 3 days); and (6) provision of written informed consent to participate in the study.

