#### Independent variables

The models draw on maternal demographic information and clinical data obtained at the time of eoPE diagnosis, including laboratory parameters, angiogenic biomarkers (sFlt-1/PlGF), and ultrasound findings. Below, the predictor variables used in each specific model are described in detail:

R model features: pulsatility index in the middle cerebral artery < percentile 5, gestational age at PE onset, number of antihypertensive administrated drugs, pulsatility index of the right uterine artery, previous PET model features: PlGF < percentile 5, sFlt-1/PlGF clinical classification, weight, personalized percentile of estimated fetal weight, pulsatility index of the left uterine artery, chronic hypertension and multiples of the median of the mean pulsatility index of the uterine arteriesHA model features: sFLt1 > percentile 95, PlGF clinical classification, PlGF < percentile 5

The models do not incorporate information related to the care center or socioeconomic status. They also do not include data on perinatal care; however, the study does collect the main perinatal outcomes for descriptive purposes. The complete set of variables collected for this study is detailed in Additional file 1.

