### Models’ validation strategy

An analysis will be conducted after the inclusion of the first 100 participants to perform an initial external validation of the predictive models. This validation will include both quantitative and semi-quantitative assessments:

The quantitative evaluation will focus on the diagnostic performance of the predicted risks, including the estimation of sensitivity, specificity, positive and negative predictive values, discrimination using the area under the ROC curve, calibration using the Hosmer–Lemeshow test, and clinical utility assessed through decision curve analysis.The semi-quantitative evaluation will consider clinicians’ perceptions of the information provided by the models. After reviewing the model’s information, they will be asked to answer four questions to assess the perceived usefulness and potential clinical impact of the predictions: (1) overall appreciation of the information (“I like it / I don’t like it”); (2) whether this information would have influenced their decision regarding corticosteroid administration (“No / Yes, I would have administered them earlier / Yes, I would have administered them later”); (3) whether it would have modified their management of hospitalization between diagnosis and delivery (“No / Yes, I would have extend the duration of hospitalization / Yes, I would have reduced it”); and (4) whether it would have changed their decision about the timing of delivery (“No / Yes, I would have indicated delivery earlier / Yes, I would have delayed delivery”).

Following this first phase, the ML training methodology will be replicated incorporating the information from the initial 100 cases, and the updated models will then be applied prospectively to the next 100 participants. This “re-training” methodology begins with a preprocessing stage, which includes missing-value imputation using MissForest, outlier removal, standardization of numerical variables with Standard Scaler, and encoding of categorical variables using OneHot and Label encoding [34]. Subsequently, model training is carried out using genetic algorithms within a multi-objective framework. These algorithms are non-deterministic, can be adaptive, and often benefit from parallel computation, enabling them to search for high-quality approximate solutions [35].

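### The planned evaluation names no external reference predictor, so it does not show whether the models add to the sFlt-1/PlGF ratio that every enrolled woman has

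*Protocol article*

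**What the plan says.** The primary objective (Objectives) is to "externally validate the diagnostic performance and clinical usefulness of three ML–based models". The section Models' validation strategy lists the quantitative measures: sensitivity, specificity, predictive values, area under the ROC curve, the Hosmer–Lemeshow test, and "clinical utility assessed through decision curve analysis". It gives no reference strategy for that curve. The one formal comparison, after 200 women, is a DeLong test of original against retrained models. The clinician survey is compared between the two phases.

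The article says the following about the angiogenic markers:
- Inclusion criteria require "availability of angiogenic biomarker results (sFlt-1/PlGF ratio) obtained at the time of diagnosis", within three days either way.
- The Background associates a raised ratio with onset and severity and says it "shows an inverse correlation with the time to delivery".
- The Fig. 1 legend divides the ratio into four clinical classes, the top one being ">655: high-risk of preeclampsia-related complications".
- Under Independent variables, the three HA inputs are sFlt-1 above its 95th percentile, a PlGF class, and PlGF below its 5th percentile. T takes PlGF below its 5th percentile and the ratio class among seven inputs. The simplified R model takes no angiogenic input.

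**The concern.** Absolute accuracy and a decision curve against flagging everyone or no one show whether a model is better than ignoring all information. They do not show whether it is better than information already on record. Here one competing predictor is measured in every woman by design, and the article itself treats it as informative about the outcomes that the models predict.

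The question is sharpest for HA, which contains no clinical or ultrasound predictor. It also arises for R: its simplified version uses no angiogenic marker, and it decides whether HA and T are displayed at all (Workflow). The Discussion foresees randomised trials of model-informed management. Without the comparison, such trials could be launched for a tool whose gain over the marker is unknown.

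**Working it through.** **Inputs.** Sensitivity and specificity of the simplified models (Background): R 60%/74%, T 68%/86%, HA 92%/52%. Incidences (Sample size estimation): R 0.4, T 0.5, HA 0.2. These incidences reproduce the article's own sample sizes:
- T: 7 × 10 / 0.5 = 140
- R: 5 × 10 / 0.4 = 125
- HA: 3 × 10 / 0.2 = 150

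**HA in all women, ignoring the R > 0.5 gate.**
- Flagged: 0.2 × 0.92 + 0.8 × 0.48 = 0.184 + 0.384 = 0.568.
- Positive predictive value: 0.184 / 0.568 = 0.324.

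**Net benefit** at threshold t is sens × prev − (1 − spec) × (1 − prev) × t/(1 − t). The article sets no threshold; 10% is chosen for illustration, so t/(1 − t) = 1/9.
- HA: 0.184 − 0.384/9 = 0.141.
- Flag all: 0.2 − 0.8/9 = 0.111.
- Flag none: 0.

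**Range of thresholds at which HA beats both defaults.**
- Lower limit: odds (0.08 × 0.2)/(0.52 × 0.8) = 0.0385, so t is about 0.04.
- Upper limit: odds 0.184/0.384 = 0.479, so t is about 0.32.
- The same calculation gives about 0.27 to 0.61 for R and about 0.27 to 0.83 for T.

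**What this implies.** For a yes/no rule, net benefit depends only on sensitivity, specificity, incidence and threshold. A ratio cut-off at 92%/52% would therefore also score 0.141 at the 10% threshold. A curve showing only the two defaults would not reveal this.

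**Precision of a paired comparison.** Assumptions not in the article: reference AUC 0.70, model AUC 0.75 or 0.80, correlation between the two AUCs 0.3 to 0.9, Hanley–McNeil variances.

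| Model | Women | Events | 95% half-width of AUC difference |
|---|---|---|---|
| HA | 100 | 20 | 0.06 to 0.16 |
| HA | 200 | 40 | 0.04 to 0.11 |
| R | 200 | 80 | 0.03 to 0.09 |
| T | 200 | 100 | 0.03 to 0.08 |

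For HA, power to detect a true gain of 0.10 runs from 24% to 90% with 100 women, and from 43% to above 99% with 200. The 200-woman rows apply to the original models. The retrained models have only the second 100 women as unused data.

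**The case against.** The strongest reply is that this is an omission in a condensed article. The strategies drawn on a decision curve are often left to the analysis plan, and nothing here excludes the ratio. The objective is to validate existing models, not to prove superiority, and the comparison with standard management is left to later trials. This stands in part: the article makes no false statement, and a separate plan may name references. But the article does list its analyses and does fix the one formal comparison. Usefulness is a primary objective now, and later trials presuppose the answer.

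Some stronger readings are tempting, but the article does not support them.
- *No comparator at all.* Original and retrained models are compared, and the survey sets the output against decisions actually taken. What is missing is an external predictor. The survey records opinion after delivery and cannot measure added accuracy.
- *HA merely recodes the ratio.* HA uses sFlt-1 and PlGF separately, and its sFlt-1 input is defined as "Antiangiogenic marker > percentile 95 for gestational age". It is not a function of the ratio.
- *The study cannot show added value.* The data would permit it; only the stated analyses do not.
- *Any ratio cut-off with the same sum of sensitivity and specificity equals HA.* It does not. At 52%/92%, net benefit at the 10% threshold is 0.104 − 0.064/9 = 0.097, below flagging all. Both values must match.
- *The ratio performs as well as HA.* The article gives no accuracy figure for the ratio. That clinicians already act on it is an inference from the eligibility rule and the risk classes.

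**Conclusion.** The concern holds as a gap in the stated analyses. They would support a claim that the models discriminate and beat flagging all or none, but not a claim that they add to the sFlt-1/PlGF ratio. The HA margin over flagging all, 0.141 − 0.111 = 0.030 at a 10% threshold, would look identical if the ratio did equally well.

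That figure is illustrative. It rests on development-phase accuracy, the assumed 20% incidence, a threshold chosen here, and use of HA in all women. In the described workflow HA runs only when R exceeds 0.5. At the stated values R flags 0.4 × 0.60 + 0.6 × 0.26 = 39.6% of women, and HA incidence in that group is not given. The figure therefore does not describe HA as deployed.

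This is an inexpensive improvement worth making before results are seen, and it does not invalidate the design. With about 20 to 40 HA events, a strict rule that usefulness may be claimed only if the model beats the ratio would be hard to defend.

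**What to change.** Pre-specify two reference predictors: the sFlt-1/PlGF ratio alone (continuous and by its existing classes), and the ratio with gestational age at diagnosis.

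- Plot their net benefit on the same decision curves as R, T and HA.
- Report each paired AUC difference with its 95% CI in the same women.
- State whether HA and T are assessed in all women or only in those with R above 0.5.
- Fit any reference coefficients in the 234-woman development cohort if the continuous ratio is available there. Otherwise use the ratio's rank for AUC and its existing classes for net benefit.
- Present the comparison as estimation, and word any conclusion on usefulness relative to this reference.

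The cost is a little more analysis on data already required for entry, with no extra participants. The conclusion may turn out less favourable to the models.

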The development process required addressing the complexity and heterogeneity of the dataset so a structured feature–selection pipeline was implemented using genetic algorithms (GAs), an evolutionary computation technique capable of efficiently searching high-dimensional feature spaces. Two complementary strategies were applied: a mono-objective GA aimed at maximizing the F1-score of each classifier, and a multi-objective GA (NSGA-II) that simultaneously optimized predictive performance and model parsimony, favouring solutions with fewer variables to enhance clinical feasibility [31]. The three models underwent internal validation and demonstrated promising diagnostic performance (sensitivity and specificity of 70%/74%, 69%/88% and 88%/69%, respectively). The R model (K-Nearest Neighbor) included twenty-five predictive variables, the T one (Logistic Regression) included fourteen, whereas the HA (Logistic Regression) incorporated thirteen. Subsequently, simplified versions of the models were derived from the multi-objective strategy: based on only five, seven and three features, achieving a sensitivity of 60%/68%/92% and a specificity of 74%/86%/52% (Fig. 1) [30]. Although the HA model prioritizes sensitivity over specificity, this trade-off may be clinically acceptable, particularly between 30 + 0 and 33 + 6 weeks of gestation, when the maternal risks of continuing the pregnancy increase while neonatal outcomes improve rapidly with gestational age.

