### Sample size estimation

We will evaluate 5 candidate predictors for the R model, 7 for the T model, and 3 for the HA model as specified in Fig. 1. Following the recommendation of having at least 10 events per predictive variable and assuming that:

Approximately 50% of women with eoPE deliver within ≤ 7 days [14], the required sample size to validate the T model is: 7 (predictive features) x 10 (events) / 0,5 (event incidence) = 140 eoPE casesApproximately 40% of women with eoPE experience any PE-related complication, and in 20% these complications include placental abruption or HELLP syndrome [30]. According to this, the required sample size to validate the R model is: 5 (predictive features) x 10 (events) / 0,4 (event incidence) = 125 eoPE cases, and to validate the HA model is: 3 (predictive features) x 10 (events) / 0,2 (event incidence) = 150 eoPE cases

This estimation assumes independence among predictor variables. However, ML techniques can identify dependencies between variables when present, which could potentially reduce the required sample size. Nonetheless, we have chosen to maintain the estimate of 200 cases, as it is the most conservative assumption and aligns with the sample size used in our previous work during model development, providing greater confidence.

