After completing recruitment of 200 patients, a final validation will be performed, formally comparing the discriminative performance of the original and retrained models using the DeLong test for paired ROC curves. Bootstrap resampling will also be considered to derive more robust confidence intervals for key performance metrics, ensuring a stable evaluation of model behavior across samples. In parallel, the semi-quantitative responses from clinicians will be compared between the two phases, providing both an objective and a subjective assessment of model performance and clinical usability.

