**Fig. 3 Fig3:**
[figure not shown]
Software architecture of the web-based application tool

**Table 1 Tab1:** Web application HTML templates and associated functionalities

HTML Template	Function
welcome.html	Displays the initial page where the clinician enters the clinical record number. Initiates the workflow that verifies or creates the REDCap™ record
principal_model.html	Main input form for the R model. Allows manual entry or prepopulation of clinical, laboratory, and ultrasound data retrieved from REDCap™
low_risk.html	Informs the clinician that the predicted risk of maternal complications is low (≤ 0.5), indicating that no additional models (HA or T) are required. Provides navigation to the post-prediction survey
submodels.html	Displayed only when the R model predicts a high risk (> 0.5). Collects the additional variables needed to run the HA and T submodels.
submodels_results.html	Presents the prediction results generated by the HA and T submodels. Provides navigation to the post-prediction survey
survey.html	Form allowing clinicians to assess the usefulness of the model outputs after reviewing the predictions
sent_survey.html	Confirmation page indicating that the clinician’s survey responses were successfully recorded in REDCap™. Provides navigation to the welcome page if the clinician wants to introduce a new patient
errors.html	Displays context-specific error messages (invalid API token, inconsistent REDCap™ records or failed data retrieval), guiding the user back to the start of the workflow

All interactions are handled by the Flask application (yellow box, Table 2), which manages routing, session states, data preprocessing, generation of clinical derived variables, prediction requests to the ML models, and communication with the REDCap™ API.

**Table 2 Tab2:** Web Application Routing Structure and associated functionalities

Route	Function
/welcome	Provides navigation to the initial page
/mrn_verification	It is triggered when the clinician enters a MRN in the initial form. Its function is to encrypt the MRN, check whether it already exists in REDCap™, and based on that, either load the corresponding data or create a new record, before redirecting the user to /r_model
/r_model	Shows the main form for the R model, prepopulated with REDCap™ data when available. Validates the API token before loading

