### Workflow

Upon accessing the application, the user enters the patient’s MRN on the welcome page. This identifier is encrypted using a one-way hash function before any query is made. The application connects to the REDCap™ database to check whether the encrypted medical record number exists.

If the encrypted medical record number exists, the corresponding record ID is retrieved and the associated data are automatically loaded into the input forms.If it does not exist, a new REDCap™ record is created with the encrypted identifier, and the forms are displayed empty for manual data entry.

After entering the clinical, analytical, and ultrasound variables, the R model provides the predicted probability of maternal complications.

If the predicted risk exceeds 0.5, the forms for the HA and T submodels are automatically displayed. Once these variables are entered, both predictions are generated, and the clinician proceeds to complete the survey. The model outputs together with the survey responses are then sent to REDCap™.If the predicted risk is lower than 0.5, the clinician is redirected directly to the survey, and the probability estimated by the R model along with the survey responses is stored in REDCap™.

Finally, the application allows the user to reset the session and initiate the workflow for a new patient.

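### One survey follows two different screens: unsplit answers cannot show whether T or HA is useful, and the steroid question lacks two needed answers

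*Protocol article*

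**What the plan says.** The protocol article (Models' validation strategy) fixes four survey questions: overall liking, steroids, hospitalization and timing of delivery. The second asks "whether this information would have influenced their decision regarding corticosteroid administration", and its only answers are no, earlier or later. No variant by type of output is described.

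What the clinician has seen beforehand depends on R. In the Web application tool section, Table 1, the page leading to T and HA is "Displayed only when the R model predicts a high risk (> 0.5"). The low-risk page tells the clinician the risk is low, "indicating that no additional models (HA or T) are required", and leads to the survey. The Workflow section confirms this: below 0.5, "the clinician is redirected directly to the survey, and the probability estimated by the R model along with the survey responses is stored".

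R, T and HA are retrained after the first 100 cases and applied to the next 100. At the end, "the semi-quantitative responses from clinicians will be compared between the two phases", as the subjective side of the assessment of performance and usability. No split by path is stated.

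Under Objectives, the primary objective names the clinical usefulness of all three models. The third secondary objective is the survey of satisfaction with the models' information for timing steroids, hospitalization and delivery.

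**The concern.** The survey records reactions to two different stimuli under one set of questions. The Background ties the timing of steroids to the seven days before birth, and T is the model for that horizon. On the R-only path T is not on screen, so a No there means something different from a No given after seeing T. One rate across both paths cannot tell the two apart.

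The phase comparison inherits the problem. Retraining can change how many women R flags, and the two phases contain different women. Either can change the mix of screens, and with it the overall Yes rate, while reactions to each screen stay the same.

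A second, separate weakness lies in question 2. A clinician who would have given steroids when none were given, or would not have given them at all, has no matching answer and must choose No or a timing option.

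What is at stake is the reading of the survey only. The accuracy results for R, T and HA are not part of this point.

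**Working it through.** **The plan's own calculation.** The article gives no share of low-risk outputs and no sample size for the survey. Its only calculation is events per variable, which reproduces: 7 × 10 / 0.5 = 140 (T), 5 × 10 / 0.4 = 125 (R), 3 × 10 / 0.2 = 150 (HA). It supplies the 40% event rate used below.

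**Inputs**
- Event rate for the R outcome: 40% (Sample size estimation).
- Version under validation: the simplified models, since "We will evaluate 5 candidate predictors for the R model, 7 for the T model, and 3 for the HA model" (Sample size estimation).
- Simplified R: sensitivity 60%, specificity 74%, the first entry of each triplet in "achieving a sensitivity of 60%/68%/92% and a specificity of 74%/86%/52" (Background).
- Full R, as a check: 70% and 74%, from "sensitivity and specificity of 70%/74%, 69%/88% and 88%/69%, respectively" (Background).
- Threshold for showing T and HA: R above 0.5.

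**Share of surveys without T or HA**

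Flagged share = prevalence × sensitivity + (1 − prevalence) × (1 − specificity).
- Simplified R: 0.40 × 0.60 + 0.60 × 0.26 = 0.240 + 0.156 = 0.396. The R-only share is 60.4%, about 60 of 100 surveys per phase and 121 of 200.
- Full R: 0.280 + 0.156 = 0.436. The R-only share is 56.4%.
- If the event rate is anywhere from 30% to 50% (assumed range), the R-only share is 57–64% with simplified R and 52–61% with full R.

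**Effect on the all-survey rate (Yes rates assumed; the article gives none)**

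All-survey rate = p × (Yes rate with T/HA shown) + (1 − p) × (Yes rate with R only), where p is the flagged share.

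| Yes rate: T/HA shown, R only | p = 30% | p = 39.6% | p = 50% | p = 60% |
|---|---|---|---|---|
| 60%, 10% | 25.0% | 29.8% | 35.0% | 40.0% |
| 50%, 20% | 29.0% | 31.9% | 35.0% | 38.0% |
| 30%, 30% | 30.0% | 30.0% | 30.0% | 30.0% |

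The rate moves only when the two paths differ. In the first row, with 100 independent surveys per phase and a two-sided 5% test (the article names no test for the survey), the shift alone would be declared a difference with probability about 12% when p goes from 39.6% to 50%, and about 33% when it goes to 60%.

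**How far p can move by sampling alone.** The standard error of p in 100 cases is √(0.396 × 0.604 / 100) = 0.0489. The 95% range is ±9.6 points within a phase, and ±9.6 × √2 ≈ ±13.6 points for the difference between phases.

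**The case against.** The strongest reply is that the all-survey rate is a proper quantity. The tool is gated by design, and the survey objective concerns the information the models provide, not T alone. If a retrained R flags more women and more clinicians then see T and HA, the usefulness of the tool per woman may really have changed. This stands. A reader might infer that the all-survey result is invalid or merely diluted; the article does not support that.

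A low-risk R output is also information. Later steroids, a shorter stay or a later delivery are natural reactions to it and are among the permitted answers. So the questions are not void on the R-only path; those surveys inform on R, but not on T or HA.

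It is also tempting to base all conclusions on steroid and delivery timing on the surveys where T and HA were shown. That goes too far. It sets aside about 60% of responses, and the flagged group in the second phase is selected by a different R, so the strata are not like for like across phases.

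Finally, a split by path is a tabulation that an analysis plan could add, the article names no pooled endpoint or test, and the additional files describing the survey section and interface are not shown. These points lower the weight of the finding. They do not remove it: the routing and the single set of questions are fixed in the article, and no later analysis can recover an answer that the form did not offer.

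**Conclusion.** The point holds in a limited form. On the article's figures about 60% of completed surveys follow an R-only screen and carry no information on how useful T or HA is. The unit is surveys and not clinicians, since a designated clinician at each centre may answer for many cases. The 60% assumes that the development sensitivity and specificity apply at the 0.5 cut-off and carry over to the new cohort.

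An unsplit phase comparison cannot separate a change in flag rate or case-mix from a change in usefulness. How much this matters depends on Yes rates by path, which the article does not give. A difference is plausible because the screens differ; with equal rates the effect is zero. A reader might infer from the illustrations that a spurious phase difference is likely. They do not show that: the chance is about 12% for a moderate shift, and about 33% for a large one under unequal assumed rates.

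The gap in question 2 follows directly from the stated answers and needs no assumption. Its frequency is unknown.

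Severity is low: the survey is a secondary, descriptive endpoint, and no accuracy result depends on it.

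**What to change.** 1. Keep the all-survey result as the summary of the gated tool.
2. Also report questions 1 to 4 by path (T/HA displayed, R only), using the R probability already stored with each survey. State the path for a probability of exactly 0.5: Table 1 calls it low risk, while the Workflow section assigns it to neither side.
3. Base statements about the usefulness of T and HA only on surveys where they were displayed.
4. Show the phase comparison by path, next to each phase's flag rate, and standardised to a common flag rate w: w × (rate with T/HA shown) + (1 − w) × (rate with R only). Note that retraining changes who falls in each path.
5. Tabulate question 2 by whether steroids were actually given. Add two answers to the form: would have given them (none were given), and would not have given them. Collapse to No/Yes for comparison with earlier surveys.

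**Cost.** Items 1 to 4 need no new data. The price is precision: about 40 surveys with T/HA and 60 with R only per phase. At a 50% Yes rate the 95% half-width is 1.96 × √(0.25/40) ≈ 15 points and 1.96 × √(0.25/60) ≈ 13 points, against about 10 points for all 100. Item 5 is a small change to a form already in use since recruitment began in October 2024. Early surveys will lack the new answers, and some clinicians may have chosen No where a new answer would have fitted, so the No/Yes bridge is approximate. The date of the change should be recorded.
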